## Abstract

**Background:**

Suicide attempt among adolescents is a public health problem around the world. The risk of recurrence is high: about 30 % of adolescents. New ways to prevent suicide attempt recurrence being developed for adult suicide attempters include maintaining contact with them, and results are encouraging.

**Methods/Design:**

The MEDIACONNEX study will be a simple blinded, parallel-group, multicenter randomised controlled trial. It will compare usual care alone to a program based on usual care plus short message service (SMS) provided to adolescents who attempt suicide and who receive treatment in pediatric and adolescent psychiatry units at hospitals in eastern France. Adolescents will be recruited over an 18-month period. The intervention will be based on the SMS, involving personalized and evolving text messages, sent on days 7 to 14 and months 1, 2, 4 and 6 after the SA. The primary endpoint will be the recurrence of an SA, with an assessment during 12 months. Secondary endpoints will be the evolution of 1) social networks, 2) depression and 3) health-related quality of life, with an assessment at inclusion and at 6 months.

**Discussion:**

This paper describes the design of MEDIACONNEX, which will assess the effectiveness of an SMS program for adolescent suicide attempters on SA recurrence. This program will be easy to reproduce and inexpensive.

**Trial registration:**

The study was registered at ClinicalTrials.gov (no. NCT02762734) on March 2016.

## Background

In industrialised countries, the incidence of suicide attempts (SAs) among adolescents 10–19 years old [1] is estimated to be at 7 to 9 % [2, 3]. Almost one third of these adolescents will make another SA within 1 year. A previous SA may be “an independent and powerful predictor of future attempts”. This “crescendo model of suicidality” concept was developed by Wong [4]: once an SA occurs, the risk of another attempt is increased. Moreover, one of the risk factors of SAs is a first attempt, in particular during the year preceding the attempt. To prevent suicide, we must prevent SAs and particularly their recurrence.

In general, research of adolescent suicide attempters has focused on risk or protective factors [5–7]. However, despite knowledge of these characteristics, the rate of SA recurrence has not decreased. So, care proposals must be creative to limit the recurrence. These last decades, new ways to prevent SA recurrence are being developed for adult suicide attempters. These new ways may be divided into 2 categories: intensive and connectedness care [8]. Intensive care includes specific therapies such as cognitive-behaviour or dialectical behavior therapy [9–12], partial hospitalization [13], and brief psychological interventions at patients’ homes [14]. With some of these treatments, the rate or recurrence has decreased: SA recurrences were reduced 50 % with than without dialectical behavior therapy [11] and the same trend was found in the Weinberg or Fonagy study [12, 13]. Connectedness care involves keeping in touch with patients and encouraging them to call in case of crises in order to avoid the SA recurrence. Motto et al. were pioneers in the field of connectedness care at the end of the 1970s by sending letters to suicide attempters at a regular frequency after the SA [15]. The care may also involve sending postcards [16, 17], making phone calls [18, 19] or using short message service (SMS) [20]. As for intensive care, this care may have positive results on the rate of recurrence or the number of recurrences. In the study of Evans, risk of SA recurrence was reduced for patients who received versus did not receive postcards (odds ratio 0.64). In the Vaiva study, for patients with this care, SA recurrence was reduced 10 % as compared with others in the first 6 months after the SA. These different care modalities have diverse results depending on the sex or personality of the patient [21].

Both types of care have clinical relevance, but the connectedness care is easy to use, has low cost and seems appropriate for adolescents. Indeed, the therapeutic alliance with young patients is not easy to achieve, and intensive care might prevent them from relating to the care. Moreover, in another study in Nancy, France, being lost to follow-up by caregivers was a risk factor of SA recurrence, even 10 years after the SA [22]. Thus, keeping in touch with adolescents after an SA is important, and adolescents may easily accept the idea if presented in a medium they often use: SMS. Some MobilHealth programs have shown good results with the system for adolescents as for adults in other specialties [23, 24].

The MEDIACONNEX study proposes to assess the effectiveness of a new way of connectedness care for adolescents after an SA: it is based on SMS sent over 6 months after the SA to allow adolescents to access care more easily and so limit the risk of SA recurrence.

## Methods/Design

### Aims and hypothesis

We hypothesized that the SMS sent over a 6-month period after an SA, in addition to usual care, may increase the delay in SA reccurence. Therefore, the primary objective is to determine whether, as compared with usual care, SMS in addition to usual care can be used to keep in touch with adolescent suicide attempters to reduce the delay in recurrence of an SA. A secondary hypothesis is that the SMS received after a first SA will reduce the suicide rate.

Secondary objectives are to determine whether, as compared with usual care, SMS in addition to usual care can be used to keep in touch with adolescent suicide attempters to improve the evolution of 1) their social network, 2) depression and 3) health-related quality of life.

### Design

The MEDIACONNEX study will be a simple blinded, parallel-group multicenter randomised controlled trial (RCT) conducted in eastern France. It will compare a program of usual care plus SMS to one of usual care only provided to adolescents who attempted suicide and who receive treatment in a pediatric and adolescent psychiatry unit at a hospital in eastern France (ClinicalTrials.gov no. NCT02762734).

### Setting

Centers of inclusion will be CHU Besançon, CHU Dijon, CHR Metz-Thionville, CHU Nancy, CHU Reims, and CHU Strasbourg. The University Hospital of Nancy will supervise the study and the evaluations will be carried out by the Clinical Investigation Center.

### Participants and consent

All adolescents receiving treatment after an SA in a pediatric or psychiatric unit of participating hospitals will be eligible for inclusion. An SA is defined as “a non-fatal act in which the individual liberally causes self-injury or ingests a substance in excess of any prescribed or generally recognised therapeutic dosage” [25]. Criteria of inclusion are age 13 to 17 years and receiving treatment for an SA. Informed consent will be obtained from patients and/or their parents. Patients will be excluded if they refuse to give consent, cannot participate (somatic or understandability reasons), are incarcerated, or do not have a cell phone.

Adolescents will be recruited during a psychiatric evaluation within 24 h of admission to the pediatric or psychiatric unit of the participating hospitals.

### Randomisation

The Zelen randomisation method will be used. This method, developed in 1979, including consent from patients with evaluated care and for the other group, has been chosen for ethical and legal reasons [26–28]. This method has been preferred to others to limit the differences between the 2 groups due to the risk of intention bias from the physician on the one hand and risk of secondary interruption of participation in the group without SMS on in the other. In each participating hospital, when an adolescent suicide attempter is eligible, a member of the research team will receive a centralized computer-generated random number to allocate the patient to a group. This patient will benefit from usual care plus SMS (group MEDIA) or usual care alone (group CLASSIC). Then, this member of the research team will inform the adolescent's psychiatrist, and the psychiatrist will verify the inclusion criteria and present to the patient and the parents the design of the study for the group to which the patient has been allocated and will gather the informed consent.

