### Outcomes

The primary outcome will be the delay of SA recurrence during 12 months after inclusion in the study. The SA recurrence and date of occurrence will be collected by a member of the research team in each participating hospital.

Secondary outcomes will include evaluation and evolution for 6 months after the SA of the adolescent’s social network by using the MSPSS, health-related quality of life by using Kidscreen-27 and VSP-A, and depression by using the CES-D. The scores and their evolution will be compared between CLASSIC and MEDIA groups.

Finally, the entire process will be evaluated by a short self-report at 6 months after the SA.

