## Statistical method

The primary analyses will be conducted on an intent-to-treat basis with data for all randomised participants. A per-protocol analysis of the primary outcome, adjusted on center, will also be reported. Continuous variables will be described with mean (SD) or median (range) and categorical variables with number (%), as appropriate. The chi-square or Fisher exact test will be used for analysis of qualitative variables and Student *t* or Mann–Whitney test for quantitative variables.

Differences in primary and secondary outcomes between the 2 groups will be tested independently. No formal adjustments will be used to constrain the overall type I error associated with the secondary analyses. Secondary analysis aims to supplement evidence from the confirmatory primary analysis, and results will be interpreted in this context.

Data will by analyzed by using SAS 9.3 for Windows (SAS Inst., Cary, NC). *P* < 0.05 will be considered statistically significant.

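### Randomised patients can be removed after the psychiatrist knows the arm, which conflicts with an intent-to-treat analysis of all randomised participants

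*Protocol article*

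**What the plan says.** All places are in the Protocol article.

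- **Randomisation** names the design: "The Zelen randomisation method will be used". The reason given is to limit differences between the groups that could arise from the physician's intentions or from patients without SMS leaving the study.
- The same section fixes the order of steps. First, "when an adolescent suicide attempter is eligible, a member of the research team will receive a centralized computer-generated random number to allocate the patient". Next, "Then, this member of the research team will inform the adolescent's psychiatrist". After that, "the psychiatrist will verify the inclusion criteria and present to the patient and the parents the design of the study for the group" (meaning the arm already drawn), and consent is sought.
- **Participants and consent** gives two inclusion criteria (age 13 to 17 and treatment for a suicide attempt). It then lists the exclusions: "Patients will be excluded if they refuse to give consent", followed by inability to take part for somatic or comprehension reasons, incarceration, and having no cell phone.
- **Statistical method** defines the primary analysis: "The primary analyses will be conducted on an intent-to-treat basis with data for all randomised participants".
- **Sample size calculation** raises 92 per group to 112 for loss to follow-up. It attributes none of the increase to refusal after randomisation.

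**The concern.** Consent is sought only after allocation, so every refusal comes from a patient who has already been randomised. The exclusion rule removes that patient, yet the analysis claims to include everyone randomised. Read literally, the two rules conflict.

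The removal is also not blind to the arm. The psychiatrist who verifies criteria and seeks consent knows the group, and each family hears only the design for its own group. MEDIA families are asked to accept text messages and CLASSIC families are not, so both the rate of refusal and the kind of patient who refuses can differ between arms.

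Randomising before consent protects the comparison only if refusers are kept in the arm they were allocated. If they are dropped, the groups analysed are no longer the groups that were randomised, and the primary hazard ratio can move away from 1 without any effect of the messages. Later analysis cannot repair this, because patients removed without consent to follow-up have no outcome data.

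**Working it through.** **1. The rules side by side.** Order under Randomisation: number drawn, psychiatrist told the arm, inclusion criteria verified, arm-specific consent sought. Rule under Participants and consent: refusal means exclusion. Rule under Statistical method: all randomised are analysed. A patient who is randomised and then refuses is excluded under the second rule and included under the third.

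**2. The plan's own figures, used as a yardstick.** Inputs from Sample size calculation: HR 0.66, alpha 5% (two-sided assumed), power 80%, 1:1 allocation.

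- Events = 4 × (1.960 + 0.842)² / (ln 0.66)² ≈ 182.
- With a 3-month control median, 18 months' accrual and 12 months' further follow-up, this gives 91.7 to 94.2 per group, depending on whether the HR is entered as 1/0.66 or 0.66. The stated 92 reproduces.
- 92 / 0.90 gives 103, not 112. Whatever explains the difference, the text does not assign it to refusal.

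**3. Effect of unequal exclusion with no true SMS effect.** The 30% one-year recurrence comes from Sample size calculation. The excluded share r and the recurrence q among those excluded are assumptions, because the article gives neither.

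Rate among those remaining in an arm = (0.30 − r × q) / (1 − r). Apparent HR = ln(1 − rate in MEDIA) / ln(1 − rate in CLASSIC).

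| r MEDIA / CLASSIC | q | Rate MEDIA | Rate CLASSIC | HR | HR with arms swapped |
|---|---|---|---|---|---|
| 15% / 5% | 45% | (0.30 − 0.0675)/0.85 = 0.2735 | (0.30 − 0.0225)/0.95 = 0.2921 | 0.93 | 1.08 |
| 20% / 5% | 50% | (0.30 − 0.10)/0.80 = 0.2500 | (0.30 − 0.025)/0.95 = 0.2895 | 0.84 | 1.19 |
| 20% / 5% | 60% | (0.30 − 0.12)/0.80 = 0.2250 | (0.30 − 0.03)/0.95 = 0.2842 | 0.76 | 1.31 |

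On the log scale these shifts are 19%, 41% and 65% of the planned effect, ln 0.66 = −0.416.

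**4. A second set of assumptions.** Half the patients have 45% risk and half 15% (average 30%), 112 are randomised per group, and exclusions occur in MEDIA only.

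- 20% of the high-risk half lost: the high-risk share falls to 0.40/0.90 = 0.444, risk is 0.283, HR 0.93, type I error about 6%.
- 40% of the high-risk half lost: share 0.30/0.80 = 0.375, risk 0.2625, HR 0.85, type I error about 9%.
- 50% of the high-risk and 10% of the low-risk half lost: share 0.25/0.70 = 0.357, risk 0.257, HR 0.83, type I error about 10%.

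If CLASSIC is the arm that loses patients, each HR inverts.

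**5. Cost of keeping SMS decliners in MEDIA.** Assume 30% recurrence without SMS, 1 − 0.70^0.66 = 20.97% with SMS, and no benefit in decliners.

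- 10% decline: risk = 0.9 × 0.2097 + 0.1 × 0.30 = 0.2188, HR = ln(0.7812)/ln(0.70) = 0.692, events needed 232.
- 20% decline: risk = 0.8 × 0.2097 + 0.2 × 0.30 = 0.2278, HR = ln(0.7722)/ln(0.70) = 0.725, events needed 304.

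Both compare with 182 events at HR 0.66.

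**The case against.** **Consent after allocation is the declared design.** This stands. The article chooses the Zelen method openly, gives reasons and seeks consent in both groups. The order of consent is not the fault. The fault is excluding refusers while describing the analysis as covering all randomised.

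**Patients are already eligible when the number is drawn.** This stands in part. The wording implies a prior screen, and the later check names only the inclusion criteria, which are age and treatment for an attempt. A reader might infer that the comprehension and cell-phone exclusions are first judged with the arm known. The text does not say so. Nor does it say that the later verification cannot remove a patient.

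**The word participants may mean those who consented, and set definitions belong in the analysis plan.** A fuller plan may well define the sets, and its absence here is not held against the trial. But the article itself states both the exclusion and the name of the set. If only consenting patients are meant, the set is a modified one and the label is wrong. The selection by arm remains in either case.

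**The bias need not favour MEDIA.** This stands. A reader might infer that removing reluctant, high-risk MEDIA patients flatters the intervention. That assumes both which arm loses more and who refuses. The only retention worry the article voices concerns the group without SMS. It is about later drop-out rather than refusal, but it points the other way.

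**Endpoint recording.** A reader might also infer that whoever holds the allocation records recurrence, from "The SA recurrence and date of occurrence will be collected by a member of the research team in each participating hospital", and that this contradicts Setting, which gives evaluations to the Clinical Investigation Center. The article does not say it is the same team member, and it does not define those evaluations, so no contradiction is shown.

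**Conclusion.** The point holds as a conflict between stated rules and as an open route to selection bias in the primary comparison. It is not a demonstrated bias of known size or sign. Under the assumed exclusions (5% against 15–20%, with 45–60% recurrence among those excluded), the apparent HR with no true effect is 0.76–0.93 if MEDIA loses more patients and about 1.08–1.31 if CLASSIC does. The outer values need a fourfold difference in exclusion and excluded patients at twice the average risk, so they are bounds for illustration and not expectations. With equal exclusion of similar patients in both arms, the HR stays at 1 and only the label of the analysis set is wrong. Ethics and permissions says inclusions are about to begin, so this should be settled first.

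**What to change.** 1. Complete and record every criterion under Participants and consent, other than consent itself, before the random number is requested. Allow no removal for eligibility afterwards.
2. Keep the Zelen order, but separate consent to follow-up and data use from consent to receive SMS. Analyse MEDIA patients who decline the messages but accept follow-up in MEDIA.
3. Where all data use is refused, call the set what it is (randomised and consenting to data use). Report refusals by arm and add a sensitivity analysis that bounds the effect of the missing patients.

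**Cost.** One step moves earlier, the consent form is revised, and the ethics body is notified before inclusions start. Keeping decliners in MEDIA also dilutes the effect: the expected HR goes from 0.66 to about 0.69 if 10% decline and about 0.725 if 20% do. The events needed for 80% power rise from 182 to 232 and 304. The decline rates are assumptions and should be replaced by the trial's own estimate.

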### Procedure

The physician will collect data on sociodemographic characteristics, previous SA, psychiatric disease (anxiety, depression etc.) and treatments.

### Intervention

The MEDIA group will receive a “keeping in touch” intervention involving the SMS. The patient will receive 6 SMS items during 6 months after the SA, the first one 7 days after the SA and the last one at 6 months (Fig. 1).

**Fig. 1 Fig1:**
[figure not shown]
Design of the MEDIACONNEX study. Legends: D = day; M = month; SA = suicide attempt; SMS = short message service

The first SMS will be sent soon after the SA because studies of adult suicide attempters underline the importance of an early start for connectedness measures.The SMS for this purpose was developed in a focus group of peers and adolescents. A pilot study was carried out in 2015 (MEDIADO, manuscript submitted) to refine the content of the SMS. The SMS item will be sent automatically from a computerized program and will change over the follow-up. The items will be personalized with the surname and genre of the patient and name of the psychiatrist or the immediate superior who meets the patient after the SA. The phone number of the unit will be included in the message and patients will be encouraged to call whenever they need to. The message will specify that someone will be always present for the patient.

Participants of both groups (MEDIA and CLASSIC) will receive usual care, and 4 self-reports will be completed by participants, at inclusion and at 6 months, to evaluate the evolution of the scores for perception of the social network (Multidimensional Scale of Perceived Social Support [MSPSS]), health-related quality of life (Kidscreen-27; Vécu et Santé Perçue des Adolescents [VSP-A]) and mood disorder (Center for Epidemiologic Studies Depression Scale [CES-D]).The MSPSS is a 12-item self-reporting questionnaire related to the participant’s social network with 5 possible answers for each item. It assesses perceptions of social support from family members, friends, and significant others. It has been used in other countries [29, 30] and was translated and validated in French by a team in Toulouse [31]. The 3 subscales, each addressing a different source of support, were identified and found to have strong factorial validity. The MSPSS had also a good internal and test–retest reliability and moderate construct validity. High levels of perceived social support are associated with low levels of depression and anxiety.

The Kidscreen-27 is a 27-item self-reporting health-related quality-of-life questionnaire developed by a European group [32] and validated in 12 European countries. It evaluates physical wellness, psychological wellness, relationships with parents, the social network, relationships with friends, and schooling. The internal consistency is good and the instrument has good discriminating power.

The VSP-A is a French-language, 37-item self-reporting, health-related quality-of-life questionnaire with 10 dimensions. This instrument has a good internal consistency and good construct validity and content validity [33].

The CES-D is a 20-item self-report on depression, validated in French for adolescents. This instrument has a good internal consistency [34, 35].

### Control intervention

Patients will receive usual care.

### Outcomes

The primary outcome will be the delay of SA recurrence during 12 months after inclusion in the study. The SA recurrence and date of occurrence will be collected by a member of the research team in each participating hospital.

Secondary outcomes will include evaluation and evolution for 6 months after the SA of the adolescent’s social network by using the MSPSS, health-related quality of life by using Kidscreen-27 and VSP-A, and depression by using the CES-D. The scores and their evolution will be compared between CLASSIC and MEDIA groups.

Finally, the entire process will be evaluated by a short self-report at 6 months after the SA.

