## Sample size calculation

The sample size of this study was calculated by using data from earlier studies [4, 5]. With one control per experimental subject, an accrual interval of 18 months, and additional follow-up after the accrual interval of 12 months, an alpha risk of 5 % and power of 80 %, assuming 30 % SA recurrence in the first year after an SA and median SA recurrence at 3 months, and an estimated hazard ratio of 0.66, we will need 92 subjects in each group. Assuming 10 % lost to follow-up, we will aim to enroll 112 subjects in each group. This sample size was calculated by using Power Sample Size v3.0.43 for Windows.

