### Primary outcome analysis

To identify differences in SA recurrence, a time-to-event analysis with Cox regression modeling will be used. The study period will be up to 12 months after the SA of inclusion. Patients without another SA, who die, or who are lost to follow-up will be censored. Patients with and without an SA during the study period will be compared between the MEDIA and CLASSIC groups. Factors associated with SA recurrence will be compared by log rank test, with *p* < 0.05 considered statistically significant. Cox proportional hazards modelling of SA recurrence will include sex, group and other variables with *p* < 0.2 on univariate analysis (i.e., explanatory variables). The score obtained from the CES-D at the time of inclusion will be considered an explanatory variable. This method will allow for considering a confusion factor and determining which initial characteristics are significant risk factors for recurrence of SA. Hazard ratios (HRs) and 95 % confidence intervals (95 % CIs) will be calculated to indicate the probability of SA recurrence by characteristics entered in the model. We will test for interactions between the included variables. Each variable will be checked for proportionality assumption by a graphical method and the Moreau method, and variables not meeting proportionality will be used for stratification [36].

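### The 92 per group is computed with 12 to 30 months of follow-up per patient, but the primary endpoint and its analysis stop every patient at 12 months

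*Protocol article*

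**What the plan says.** Three places in the protocol article describe the endpoint window, and all give 12 months.

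- Abstract, Methods/Design: "The primary endpoint will be the recurrence of an SA, with an assessment during 12 months". No time origin is given.
- Outcomes: "The primary outcome will be the delay of SA recurrence during 12 months after inclusion in the study".
- Primary outcome analysis: "The study period will be up to 12 months after the SA of inclusion". Patients with no further suicide attempt (SA) are censored.

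No section plans to record or analyse recurrence beyond 12 months in any patient.

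The Sample size calculation takes a different follow-up as input: "an accrual interval of 18 months, and additional follow-up after the accrual interval of 12 months". Its other inputs are 1:1 allocation, "an alpha risk of 5 % and power of 80" %, "assuming 30 % SA recurrence in the first year after an SA", "median SA recurrence at 3 months" and a hazard ratio of 0.66. It arrives at 92 per group and raises this to 112 for 10 % loss.

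**The concern.** In a survival sample size, an accrual period plus an additional follow-up period means that each patient is observed from entry to a common closing date. With 18 months of accrual and 12 more months, the first recruit contributes 30 months, the last 12, and the average under uniform accrual is 21. The endpoint rule censors everyone at 12 months. Any event that the calculation expects after month 12 cannot occur in the analysis, so the number of patients needed for the required events is understated.

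At stake is whether 92 per group gives the claimed 80 % power for the endpoint as defined. How much is lost depends on how many recurrences are expected after month 12, and so on which event-rate assumption drives the calculation.

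**Working it through.** **Inputs.** From the Sample size calculation: hazard ratio (HR) 0.66, alpha 5 %, power 80 %, 1:1 allocation, accrual A = 18 months, additional follow-up F = 12 months, median 3 months, 30 % recurrence at one year, 92 and then 112 per group. Assumed here: two-sided test, exponential times, uniform accrual, loss treated as removing 10 % of patients. The text does not say which arm the 3-month median belongs to, so both orientations are shown.

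**Step 1. Events needed (Schoenfeld).**
D = 4 × (1.96 + 0.84)² / (ln 0.66)² = 181.8, rounded up to 182.

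**Step 2. Event probability per patient.**
- Closing-date design: P = 1 − exp(−λF) × (1 − exp(−λA)) / (λA).
- Fixed 12 months: P = 1 − exp(−12λ).
- Number per group: n = (D/2) / mean P = 90.9 / mean P.

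**Step 3. Reproduce the stated figure, then change only the window (3-month median).** Orientation 1 gives the slower arm a 3-month median and the other arm 0.66 × 3 = 1.98 months. Orientation 2 gives the control arm 3 months and the SMS arm 3 / 0.66 = 4.55 months.

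| Orientation | Window | P in the two arms | n per group |
|---|---|---|---|
| 1 | 12–30 months | 0.998, 0.985 | 91.7 → **92** (the stated figure) |
| 1 | fixed 12 months | 0.985, 0.938 | 94.6 → **95** |
| 2 | 12–30 months | 0.985, 0.945 | 94.2 → 95 |
| 2 | fixed 12 months | 0.938, 0.840 | 102.3 → **103** |

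Of these four, only the 12-to-30-month window in orientation 1 returns 92. A fixed 12 months does not return it in either orientation. The longer window is thus a working input to the published number.

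**Step 4. Power under the 12-month cap.** Power = Φ(√d × |ln 0.66| / 2 − 1.96), where d is the expected number of events.

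| Analysed per group | Orientation 1 | Orientation 2 |
|---|---|---|
| 92 | d = 176.9, 78.9 % | d = 163.5, 75.7 % |
| 100.8 (112 × 0.9) | d = 193.8, 82.4 % | d = 179.1, 79.4 % |

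The margin exists because 112 exceeds what a 10 % allowance on 92 requires: 92 / 0.9 = 102.2, i.e. 103.

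**Step 5. Same comparison with 30 % at one year as the control rate.** λ = −ln(0.7) / 12 = 0.0297 per month.
- 12–30 months: P = 0.458 and 0.334, so n = 90.9 / 0.396 ≈ 230 per group.
- Fixed 12 months: P = 0.300 and 0.210, so n = 90.9 / 0.255 ≈ 357 per group.

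This input does not yield 92 on either window. Its conflict with the 3-month median is a separate problem in the same section.

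**Step 6. Time origin.** The Outcomes section counts from inclusion and the analysis section from the index SA. Recruitment is fast: "Adolescents will be recruited during a psychiatric evaluation within 24 h of admission to the pediatric or psychiatric unit of the participating hospitals". Moving the end of the window by 1 to 7 days changes the expected count by about 0.1 to 1.1 events among 224 patients (224 × the probability of an event in those days, using either event rate).

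**The case against.** The strongest reply is that the error is small and already covered. On the 3-month median nearly all modelled recurrences fall within 12 months, so the cap adds only 3 patients per group in the orientation that reproduces 92 (8 in the other, before rounding). The 112 target, less 10 %, still gives about 79 to 82 % power. This stands, and it limits the point to a correction of the sizing.

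One could also say that 18 plus 12 months merely describes the calendar, since the last recruit finishes at month 30 under a fixed 12-month window too. As a description of the calendar that is right. As an input to the calculation it is not, because the stated 92 is recovered only when early recruits are credited with more than 12 months.

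Three stronger readings are tempting, and the document does not support them.

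- *Three incompatible windows.* Every description of the endpoint ends at 12 months, and the inclusion and SA clocks probably differ only by days. The material conflict is two-way: 12 months against 12 to 30.
- *The trial throws away follow-up data.* No section plans to collect recurrence after month 12, so nothing collected is discarded. The sizing credits observation that the endpoint does not use.
- *Following everyone to the closing date would give 55 % more events.* With 112 per group, 30 % at one year and no loss, the sums are right: 57 against 89 events. But they need a constant hazard and HR 0.66 out to month 30, two years after the last SMS at month 6, and they are not the basis of the 92. Suppose instead that the 3-month median applies to those who recur, with 30 % recurring by month 12. Then the eventual control proportion is 0.30 / (1 − 2⁻⁴) = 32 %, the SMS arm reaches at most 22.5 %, and unlimited follow-up gives 112 × (0.320 + 0.225) ≈ 61 events, about 7 % more than 57.

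A fixed 12-month endpoint after a 6-month intervention is legitimate. Extending observation would change the question and is not needed to remove the inconsistency.

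**Conclusion.** The point holds as an inconsistency between the sizing and the endpoint. The Sample size calculation rests on 12 to 30 months of follow-up per patient; the endpoint and its analysis allow 12.

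On the protocol's own 3-month median, a fixed 12-month follow-up raises the requirement from 92 to about 95 per group, or to about 103 if that median is the control arm's. Power at 92 is about 76 to 79 % rather than 80 %. At the planned 112 less 10 %, it is about 79 to 82 %, so enrolment largely absorbs the difference.

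The window becomes important if the 30 % one-year rate is taken as the sizing input: about 230 against about 357 per group. The choice of window should therefore be settled together with that separate conflict.

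These figures assume a two-sided test, exponential times, proportional hazards and uniform accrual. The orientation of the hazard ratio in the software is inferred from the match to 92; the text does not state it. The wording of the time origin is a minor matter.

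**What to change.** Recompute the Sample size calculation with a fixed 12-month follow-up for every patient, and restate either the number required or the power at the planned enrolment. State which arm the 3-month median describes, because that decides between about 95 and about 103. With the 10 % loss allowance these become 95 / 0.9 → 106 and 103 / 0.9 → 115 per group, against the planned 112. Keep the 18-month accrual period as a calendar statement, not as a source of extra follow-up.

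Use one time origin, defined once, in both the Outcomes and the Primary outcome analysis sections.

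The cost is one recalculation and a few words. On the 3-month median, enrolment changes by at most 3 per group, or stays at 112 with the power restated. If the recalculation uses the 30 % rate instead, the required number rises far above 112, and that consequence belongs to the separate conflict between the two event-rate inputs. The article's Ethics and permissions section says that inclusions had not yet begun, so the correction could be made before recruitment.
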